***Secondary parameters***						
Evaluation of PRIMARY*	UMUX Modified CSQ-8				X	
	Questions developed for the study					
***Other parameters***						
Demographics	Developed for study		X			
Concomitant treatment	Developed for study		X		X	X
BPD symptoms	SCID-II BPD PQ	X				
BPD behavior	BSL-23		X		X	X
Achievement of developmental milestones	DML		X		X	X
Life experiences	Modified LES		X		X	
Psychopathology	SPSY		X		X	X
Alternative Model for Personality Disorders	LPFS-BF PID-5-BF		X		X	X
Impulsivity	S-UPPS		X			
Internalizing problems	DASS		X		X	X
Loneliness	De Jong Gierveld questionnaire		X		X	X
Motivation for change	MYTS		X		X	X
Quality of life	ReQoL		X		X	X
Impact of COVID-19	Developed for study		X		X	X

**Only filled out by participants in the intervention group*

ESM = Experience Sampling Method, DERS-18 = Difficulties in Emotion Regulation Scale, NRI-BSV = Network of Relationships Inventory – Behavior Systems Version, UMUX = Usability Metric for User Experience, CSQ = Client Satisfaction Questionnaire, SCID-II BPD PQ = BPD section of the Structured Clinical Interview for DSM-IV Axis II disorders Personality Questionnaire, BSL-23 = Borderline Symptom List, DML = Developmental Milestones List, LES = Life Experiences Survey; SPSY = Screeningsinstrument Psychische Stoornissen, LPFS-BF = Levels of Personality Functioning Scale 2.0 Brief Form, PID-5-BF = Personality Inventory for DSM-5 Brief Form, S-UPPS = UPPS-P impulsive behavior scale short version, DASS = Depression Anxiety Stress Scales, MYTS = Motivation for Youth Treatment Scale, ReQoL = Recovering Quality of Life

#### ESM-questionnaire

An ESM-questionnaire with 22–25 questions was developed for the purpose of the PRIMARY study. Recommendations to enhance the feasibility of an ESM-intervention in young people were taken into account in this process, like tailoring the first assessment to correspond to the young person’s sleep schedule [43]. The questionnaire is included in the Supplemental Material.

The daily ESM-questionnaire covers activities, relational support and conflict, emotions, substance use and, at the end of the day, functioning. The questions regarding emotions were informed by similar research [44] and the Positive And Negative Affect Scale (PANAS) [45]. One question regarding applied adaptive emotion regulation strategies is included, informed by Safety Planning Intervention [46]. Additionally, a question on self-harming thoughts and behaviors since the last notification is included. Answers are provided via a multiple choice format or on a Likert-scale ranging from 1 (*not at all*) to 7 (*very much*).

#### Main study parameters

**Self-Harming Thoughts and Behaviors.** Five questions were formulated to assess frequency and severity of self-harm, these are included in the Supplemental Material.

**Emotion Regulation.** The 18-item Difficulties in Emotion Regulation Scale (DERS-18) [47] is included. The DERS-18 comprises six subscales: ‘lack of emotional awareness’, ‘lack of emotional clarity’, ‘difficulty engaging in goal-directed behavior’, ‘impulse control difficulties’, ‘nonacceptance of emotional responses’, and ‘limited access to emotion regulation strategies’. Items are answered on a 5-point Likert scale. The scale has adequate construct and predictive validity, and good test-retest reliability [47].

**Quality of Relationships.** Participants fill out the 11-item version of the Network of Relationships Inventory – Behavior Systems Version (NRI-BSV) [48] regarding one parent and a best friend. The NRI-BSV comprises two subscales: ‘support’ and ‘negative interactions’. Items are answered on a 5-point Likert scale. The questionnaire was validated and the factor structure was confirmed [48].

#### Secondary parameters

**Evaluation of PRIMARY.** Participants in the intervention group rate usability of the ESM-element of PRIMARY on the 3-item Usability Metric for User Experience (UMUX) [49] on a 7-point Likert scale. This questionnaire correlates well with the original, longer version, is reliable, and the items load on one underlying factor [49]. Overall satisfaction with PRIMARY is indicated via a modified 4-item version of the Client Satisfaction Questionnaire-8 (CSQ-8) [50].

Included in the Supplemental Material are the modified version of the CSQ-8, two additional items regarding the duration and frequency of the ESM-questionnaire, and 10 questions assessing the clinician’s impression of the young person after the study.

#### Other parameters

Information regarding demographic characteristics and concomitant treatment is collected. BPD related pathology is measured via the BPD section of the Structured Clinical Interview for DSM-IV Axis II disorders Personality Questionnaire (SCID-II BPD PQ) [51], and the behavior scale of the Borderline Symptom List (BSL-23) [52]. Achievement of developmental milestones is measured via the Developmental Milestones List (DML) [53], which comprises 13 items regarding developmental tasks that young people face when growing up, making up three subscales: personal, social and academic functioning. Items are answered on a 7-point Likert scale. Life experiences are assessed with a shortened version of the Life Experiences Survey (LES) [54]. Psychopathology is measured with a Dutch questionnaire called Screeningsinstrument Psychische Stoornissen (SPSY) [55], which is based on the Strengths and Difficulties Questionnaire (SDQ) [56]. The brief form of the Levels of Personality Functioning Scale 2.0 (LPFS-BF) [57] and Personality Inventory for DSM-5 (PID-5-BF) [58, 59] are included as measures of the Alternative Model of Personality Disorders [60]. Impulsivity is measured with the short version of the UPPS-P impulsive behavior scale [61]. Internalizing problems are measured with the Depression Anxiety Stress Scales (DASS) [62]. Loneliness is assessed with the short version of the Dutch De Jong Gierveld questionnaire [63]. Motivation for change is measured by the Motivation for Youth Treatment Scale (MYTS) [64]. The 11-item version of the Recovering Quality of Life (ReQoL) [65] concerns functioning over the past week, and is answered on a 4-point Likert-scale. During the COVID-19 pandemic (i.e., until March 10, 2023), impact of COVID-19 on daily life was measured via six semi-structured interview questions developed for the study.

### Data management

Participants fill out the questionnaires through an online portal called ‘RoQua’. At GGz Centraal, RoQua is also used for Routine Outcome Monitoring and it is linked to the electronic patient records. Hence, the answers on the questionnaires of this study are available to clinicians through these records. The data is stored in a secure online environment. RoQua sends personalized links via text messages in which the ESM-questionnaires are embedded. RoQua is formally recognized as an instrument to carry out research in the Netherlands and operates in accordance with the European General Data Protection Regulation [66].

Data will be pseudonymized and stored on a secured network, accessible only by members of the research staff. Staff are all subject to medical confidentiality via their employment at the mental healthcare facility. Personally identifiable material, such as study consent forms, will be stored separately from research data files. Data will be stored for 20 years after completion of the trial. Data integrity will be supported by fully computerized procedures, i.e., participants answering all questionnaires via a computer or their smartphone (within the RoQua environment). Hence, the chance of data being recorded incorrectly is improbable.

### Safety considerations

As the PRIMARY study includes young people who self-harm, the participant group can be considered a higher risk population, given the inherent risk of severe bodily damage and the predictive connection of self-harm to suicide attempts [15]. Hence, careful consideration was given to the safety procedures and to imbedding this study within a safe care system. Previous ESM-studies have shown that frequently asking an individual about their symptoms, even suicidal ideation or negative emotions, does not increase the frequency of these symptoms [27, 43, 67, 68]. Furthermore, ESM was considered a promising method in the development of effective interventions for young people who self-harm [38] as it provides young people with the opportunity to monitor and intervene before self-harm occurs [69]. If acute suicidality is identified during a weekly report session or a research assessment, a structured suicide-risk-protocol will be activated. This protocol was developed in line with the Dutch guidelines regarding suicide prevention [70], and involves the RA sharing the information with a clinician at the healthcare institution who will put the necessary interventions in place.

Serious adverse events, such as events that require hospitalization, will be monitored and reported to the Medical Ethical Board Utrecht within 15 days after the sponsor’s first awareness of the event. Serious adverse events that result in death or are life threatening will be reported within seven days of first knowledge. Since serious adverse events are monitored by the Medical Ethical Board, and given the safe care system in which the study is embedded, a Data Monitoring Committee is not required.

### Data analysis plan and power calculations

Analyses that cover effectiveness of PRIMARY will be performed according to a modified version of the *intention-to-treat* principle [71], which entails including all participants with at least one data point post-baseline regardless of their compliance during the study. This way, random selection in the sample will be guaranteed which ensures the most accurate conclusions following the analyses. In the following section, analyses will be outlined for each study objective (i.e., research question) as well as the required sample size to answer the research questions based on relevant power analyses and recent literature^1^. Multiple imputation will be considered if the amount of missing values is non-trivial. The randomization stratification variable of age and gender will be examined as covariates in the analyses described below. Other covariates, such as concomitant treatment, will also be considered.

To examine the effectiveness of PRIMARY, an ANCOVA-test will be used to compare data from Wave 1 and 2 by study group (study objective 1). Specifically, the following variables will be examined: emotion regulation, quality of relationships, and self-harm. To reach a power of 0.80, the power analyses run in G*Power 3.1 [72]^2^ and R [73], with an additional correction for the pre-test as a covariate, indicated a sample size of *n* = 48 per group to be necessary to detect a medium effect size (α = 0.05). Taking into account a drop-out of 10% (based on the feasibility study), a total sample size of *N* = 106 is necessary to answer this research question.

Regarding the effect of PRIMARY on the effectiveness of subsequent specialized treatment (i.e., HYPE), an ANOVA-test repeated measures with a within-between interaction will be applied to Wave 1, 2 and 3 including only those participants receiving HYPE treatment (study objective 2). To reach a power of 0.80, a sample size of *N* = 42-106 is necessary when considering a medium-large effect size (G*Power 3.1) [72]^1^. Taking into account the 10% drop-out from the feasibility study, a sample size of *N* = 46-118 is required (i.e., young people receiving HYPE treatment).

To increase knowledge on underlying processes of self-harming thoughts and behaviors, and adaptive coping strategies on an individual level, a link between these constructs and emotions and social interactions will be examined using ESM data (study objective 3). Given the large number of measurements of the ESM-questionnaire (i.e., five times a day for 28 consecutive days per participant), these data are suitable for a single-case experimental design [74]. This design focusses on the within-component of the data and is useful for investigating individual processes over time. Additionally, these analyses will be repeated on a group-level. Given the novelty of these types of analyses, it is expected that there will be relevant developments regarding statistical models in the upcoming years. Hence, the best applicable analyses will be considered once the data is collected. Currently, Group Iterative Multiple Model Estimation (GIMME) [75] would be an appropriate type of analysis to answer this research question. For GIMME, at least 60 data points are needed from each participant to reach sufficient power [76], i.e., participants with ≥ 43% compliance would be included.

Lastly, to characterize participants’ and clinicians’ evaluation of PRIMARY (study objective 4), descriptive statistics (e.g., means, standard deviations) will be calculated on the relevant questionnaires at Wave 2.

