### Study groups

#### Intervention group

After baseline assessment (Wave 1), the intervention group starts with the PRIMARY intervention. PRIMARY is an intervention consisting of two elements: ESM and weekly, one-on-one structured report sessions based on the individual’s ESM-answers. Participants fill out the ESM-questionnaire via their smartphone five times a day for 28 consecutive days (i.e., 4 weeks). Each ESM-questionnaire appears at random times within blocks of 2.5 h periods. Participants can choose a starting time for the first block between 06:00 AM and 12:00 PM. To encourage compliance with the ESM-questionnaire protocol, motivating text messages are sent once a week. In case compliance drops below 70% during the previous three days, participants receive an extra text message to stimulate respondence (maximum of once a week). If a participant allocated to the intervention group does not have a smartphone or internet on their smartphone, they can borrow a smartphone from the research staff. The internet on this smartphone is limited to accessing the ESM-questionnaire and therefore does not change the participant’s situation regarding social interactions.

The weekly report session encompasses a 15-minute video call (or appointment at the institution on request of the participant) with the RA over the course of the ESM-procedure (i.e., four times). During these sessions, the answers provided on the ESM-questionnaire over the past week are discussed in a structured, scripted way using a graphical report in which the outcomes are summarized. These sessions aim to enhance the participant’s insight into the connection between their emotions, activities and social context.

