#### Comparison group

After baseline assessment (Wave 1), participants in the comparison group receive care-as-usual, which entails a waiting list for further care.

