### Measures

All study measures and their timing during the study are depicted in Table 1. All participants, independent of study group, fill out questionnaires at baseline (Wave 1) prior to commencing the study intervention, and at the end of the intervention phase (i.e., four weeks later; Wave 2). Participants who subsequently enroll in HYPE also fill out the questionnaires 10 weeks after starting their treatment (Wave 3). All assessments other than the ESM-questionnaire are administered to both the intervention and comparison group at the mental healthcare institution or through a video call with an RA, depending on the preferences of the participant.

**Table 1 Tab1:** Schedule of outcome measures

Construct	Measure	Screening	Wave 1	Intervention Phase	Wave 2	Wave 3
ESM-questionnaire*	Developed for study			X		

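### The modified intention-to-treat rule selects on post-randomisation behaviour, so it cannot guarantee random selection, and its data point is not tied to a wave or outcome

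*Protocol article*

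**What the plan says.** Under Data analysis plan and power calculations, the protocol article sets the population for the effectiveness analyses by a modified intention-to-treat principle, "which entails including all participants with at least one data point post-baseline regardless of their compliance during the study". It names no instrument and no wave. The next sentence claims: "This way, random selection in the sample will be guaranteed which ensures the most accurate conclusions following the analyses". On missing data it says only that "Multiple imputation will be considered if the amount of missing values is non-trivial".

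Four other places bear on what can count as a data point:

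- Measures: "All assessments other than the ESM-questionnaire are administered to both the intervention and comparison group". The ESM row of Table 1 carries an asterisk whose footnote reads "Only filled out by participants in the intervention group".
- Intervention group: "Participants fill out the ESM-questionnaire via their smartphone five times a day for 28 consecutive days".
- Comparison group: after baseline, "participants in the comparison group receive care-as-usual, which entails a waiting list for further care". The next scheduled assessment for these participants is Wave 2.
- The plan for objective 3 (ESM data), in the same analysis section, uses the same term for single ESM responses: "at least 60 data points are needed from each participant to reach sufficient power".

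Objective 1 is an ANCOVA on Wave 1 and Wave 2 scores by study group. Randomization and group allocation says that staff are not blind and that participants are blind only during the Wave 1 assessment.

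**The concern.** Randomisation protects the comparison of everyone randomised. Once people are removed because of something that happened after allocation, the protection holds only if the removal is unrelated to outcome given arm and covariates. The article asserts the protection as a property of the rule, and the rule cannot deliver it.

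Different loss by arm is plausible. Both sides know the allocation after Wave 1, one arm has frequent prompts and four report sessions, and the other waits. The wording adds a second difficulty: because ESM exists in one arm only, the literal rule sets a far lower bar for inclusion in the intervention arm than in the control arm. At stake are who is in the declared population and, depending on how missing Wave 2 scores are handled, the treatment estimate for every effectiveness outcome.

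**Working it through.** **The plan's own figure.** Assume that a medium effect means 0.5 SD, the test is two-sided and the pre-post correlation is r = 0.5. A two-sample t-test at α = 0.05 and power 0.80 needs 64 per group, and 64 × (1 − 0.5²) = 48, as stated. For the total, 96 × 1.10 = 105.6, i.e. 106 as stated; 96 / 0.90 gives 107. The sample size is not at issue, and r = 0.5 is consistent with it.

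**Who is included on the literal reading.** Each intervention participant has 5 × 28 = 140 chances to supply an ESM response. The article's 43% compliance threshold is 60/140, so a single ESM response is one data point in its own usage. Let d be the Wave 2 loss, equal in both arms, and q the share of intervention participants without Wave 2 who answered at least one prompt (q is an assumption).

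- Control inclusion = 1 − d
- Intervention inclusion = 1 − d(1 − q)

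With the expected d = 10% and 90 per arm (half of 180), controls are 81 of 90. The intervention arm is 89.1 of 90 at q = 0.9, and 85.5 to 90 for q from 0.5 to 1. The criterion differs by arm even when Wave 2 loss is identical.

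**Whether that reaches the estimate.** An ESM-only participant has no Wave 2 score.

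- Without imputation, such a participant drops out of the ANCOVA, which then uses Wave 2 completers in both arms.
- With imputation from the Wave 1 score alone, the estimate is the same as the completer ANCOVA.
- With imputation from further baseline variables, when loss depends on those variables, the literal rule gave a simulated bias of about 0.05 SD even at equal 10% loss. The direction is against PRIMARY, because the intervention arm keeps its drop-outs, who tend to be worse, while the control arm loses them.

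**Bias of the completer analysis.** Before adjustment, bias = (p1 − p0) × gap, where p1 and p0 are the losses in the PRIMARY and control arms and gap is how much worse those lost are than completers. The article gives only 10% overall. Assume 15% v 5%, which averages 10% under 1:1 allocation.

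- Gap 0.5 SD: (0.15 − 0.05) × 0.5 = 0.05 SD
- Gap 1.0 SD: (0.15 − 0.05) × 1.0 = 0.10 SD
- Equal loss and equal gap: 0

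These figures ignore the planned baseline adjustment. A simulation included it (2 million participants, no treatment effect, r = 0.5, 15% v 5% loss, those lost about 1 SD worse), with this bias in favour of PRIMARY:

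| Analysis | Bias (SD) |
|---|---|
| Raw completer difference | 0.081 |
| Planned ANCOVA on completers | 0.061 |
| All randomised, imputed by arm from Wave 1 score only | 0.061 |
| Literal ESM rule, same imputation | 0.061 |

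The raw value is below 0.10 because, under one loss mechanism, the gap is smaller in the arm that loses more. The adjusted value agrees with 0.081 × (1 − 0.5²) = 0.061. If loss depends on the Wave 1 score only, the ANCOVA bias is about zero (0.002).

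**What richer imputation gains.** Where loss depended on further baseline variables that also predict outcome, imputing all randomised participants with those variables reduced the bias from 0.04 SD to about 0.

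**The case against.** The strongest reply is that ESM plays no part in the objective 1 ANCOVA; it serves the separate ESM analyses of objective 3. The effectiveness section deals with Waves 1, 2 and 3, so a wave-level meaning of data point is natural, and an ESM-only participant contributes nothing unless imputed. Enlarging the population and imputing from the Wave 1 score changes nothing. The exact imputation model and sensitivity analyses are commonly left to an analysis plan that is not shown.

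Most of this stands, and it rules out three stronger readings:

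- A reader might infer that the ESM asymmetry itself biases the planned estimate towards PRIMARY. The documents do not support this. Without imputation the asymmetry has no effect on the ANCOVA, and where it does act it pushes the other way if drop-outs are worse. The 0.05 to 0.10 SD figures describe unadjusted completer bias, a different mechanism.
- A reader might infer that, on the Wave 2 reading, nothing is left to impute. The rule asks for one data point, not all of them. There are three primary outcomes, and the NRI-BSV is completed for a parent and a friend, so someone can qualify with some Wave 2 scores missing. Objective 2 adds Wave 3.
- A reader might treat the conditional wording on multiple imputation as an error. In a condensed article it is not.

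What the reply does not rescue is the stated guarantee, which is false on either reading, or a rule that leaves its qualifying data point undefined when the article applies that term to data collected in one arm only. Both are statements in the article, not details deferred elsewhere.

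**Conclusion.** The point holds in a limited form. Inclusion that depends on a post-randomisation event cannot guarantee random selection. Literally, the criterion differs by arm; read as Wave 2, it is close to a completer analysis. The objective 1 ANCOVA on completers is unbiased only if loss is unrelated to outcome given arm and covariates.

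The illustrative bias of about 0.06 SD is 0.06 / 0.5 = 12% of an assumed 0.5 SD target. It rests on assumed loss of 15% v 5%, those lost about 1 SD worse, and r = 0.5. It is zero with equal loss for equal reasons, about zero if loss depends only on the Wave 1 score, and larger if loss differs more between arms. None of these loss patterns is given in the article, so this shows sensitivity and is not a forecast. Severity: should be fixed.

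**What to change.** 1. Define the objective 1 population as all randomised participants, analysed in the arm to which they were allocated.
2. State that ESM responses do not determine inclusion.
3. Make multiple imputation by arm the stated method for missing Wave 2 scores, using the Wave 1 score, the other collected baseline measures and any Wave 2 measures that were observed. The Wave 1 score alone adds nothing over the completer ANCOVA.
4. Add one delta-adjusted sensitivity analysis for missing Wave 2 scores. Imputation does not remove bias from loss that depends on the unobserved outcome; this analysis shows how far the conclusion depends on it.
5. Delete the sentence claiming that random selection is guaranteed.

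The cost is some wording, a little programming and slightly wider intervals. No sample-size figure changes. The changes should be recorded before outcome data are examined by arm.

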### Objectives

The first objective of this RCT is to determine whether PRIMARY, compared to a waiting list control, is effective in improving the following outcomes: self-harm, emotion regulation, and quality of relationships. To this end scores at baseline (Wave 1) and at the end of the intervention phase (Wave 2) will be compared. The second objective is to examine the effectiveness of PRIMARY combined with subsequent specialized treatment in the early intervention program Helping Young People Early (HYPE) [41] in improving the outcomes for young people with borderline personality pathology. Scores on the specified outcome variables after 10 weeks of HYPE treatment (Wave 3) will be compared to scores at baseline (Wave 1) and at the end of the intervention phase (Wave 2) for participants who attended HYPE. The third objective is to investigate the associations between emotions, relational support and conflict, adaptive coping strategies, and self-harm using individual-level ESM data. The fourth objective is to examine the participants’ and clinicians’ satisfaction regarding the use of PRIMARY. This will be examined at the end of the intervention phase (Wave 2).

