### Ethics and dissemination

Ethical approval for this study was granted by the Medical Ethical Board Utrecht, the Netherlands (NL73936.041.20) on the 15th of July 2020. Important protocol modifications will be amended and submitted to the Medical Ethical Board Utrecht. Careful attention has been devoted to the consideration of participant privacy and confidentiality. Procedures to support privacy and confidentiality were discussed in detail with the legal department of GGz Centraal and are in line with the European and Dutch regulations on privacy [66]. Participants can withdraw their consent and stop their participation in the study at any time without providing a reason. When this is the case, the data that has been collected thus far will be used in the study, unless the participant specifically requests their data to be deleted.

The study’s protocol has been publicly registered at the International Standard Randomized Controlled Trial Number registry (ISRCTN registry; doi: 10.1186/ISRCTN42088538). The final trial dataset belongs to the sponsor (i.e., GGz Centraal). The principal investigator has access to the dataset. The trial protocol, statistical code and other relevant information will be made publicly available on an appropriate archive platform for sharing purposes (e.g., Open Science Framework) alongside the publication of the trials’ results. The dataset will be available to other researchers on request. They can send in a brief research proposal to request access to the relevant data and may report on additional findings from the study.

Major outcomes of the study will be presented in publications in international peer-reviewed journals, at academic congresses, and any other forum in a de-identified form by the principal investigator, members of the steering committee and researchers who have significantly contributed in the execution of the study (e.g., PhD candidates). Authorship eligibility for publications will be based on contribution to the study and specific manuscript, in accordance with the Contributor Roles Taxonomy (CRediT) statement [77]. Dissemination of findings will also commence in plain langue via the sponsors’ website. To promote the dissemination of findings in the clinical field, results will also be published in practice-oriented journals and presented at clinically oriented workshops and symposia.

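### The repeated-measures ANOVA named for objective 2 needs all three waves, but the plan's inclusion rule needs only one post-baseline score, and no firm missing-data method links the two

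*Protocol article*

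**What the plan says.** All of the following is in the protocol article.

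- **Inclusion rule** (Data analysis plan and power calculations). Analyses of PRIMARY's effectiveness follow a modified intention-to-treat principle, "including all participants with at least one data point post-baseline regardless of their compliance during the study".
- **Objective 2 test** (same section). "an ANOVA-test repeated measures with a within-between interaction will be applied to Wave 1, 2 and 3", restricted to participants who receive HYPE.
- **Missing data** (same section). "Multiple imputation will be considered if the amount of missing values is non-trivial". No threshold is given, and no rule says which analyses would use it.
- **Sample size for objective 2** (same section). N = 42-106, raised to N = 46-118 for 10% drop-out.
- **Timing of Wave 3** (Measures). "Participants who subsequently enroll in HYPE also fill out the questionnaires 10 weeks after starting their treatment (Wave 3".

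**The concern.** The inclusion rule and the named test cannot both be followed when a Wave 3 score is missing. A HYPE participant who has Wave 2 meets the rule. A standard repeated-measures ANOVA works on a complete person-by-wave table, so without imputation that person's Wave 1 and Wave 2 scores leave the objective 2 analysis as well.

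The rule is worded for analyses of PRIMARY's effectiveness and does not name objective 2. It is reasonable to read it as covering that objective, because the Objectives section frames objective 2 as the effectiveness of PRIMARY combined with HYPE.

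Two things are at stake. If those who lack Wave 3 differ from the rest in a way that differs by arm, the completers are no longer comparable between arms, and the group-by-wave interaction can pick up a pattern produced by selection. In addition, whether to impute would be decided once the extent of missingness is known, in a trial whose staff are not blind to allocation.

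**Working it through.** **1. The plan's own figures.** Inflating by N / (1 − 0.10) gives 42 / 0.9 = 46.7 (stated 46) and 106 / 0.9 = 117.8 (stated 118), so the drop-out step reproduces to within rounding. In reverse, 46 × 0.9 = 41.4 and 118 × 0.9 = 106.2. The objective is therefore sized on those who remain, which fits a completer analysis. The N = 42-106 before inflation could not be confirmed, because the numeric effect sizes, the correlation and the effect-size convention are not in the visible text. Nothing here depends on it being right or wrong.

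**2. Who is lost.**

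| Scores available | Meets the inclusion rule? | Enters a standard three-wave ANOVA? | Enters a mixed model? |
|---|---|---|---|
| Waves 1, 2, 3 | yes | yes | yes |
| Waves 1, 2 | yes | only if imputed | yes |
| Waves 1, 3 | yes | only if imputed | yes |

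**3. Size of the bias.** The inputs are 53 per arm (106 / 2, the upper end of the stated range before inflation), no true effect at any wave, unit SD and correlation ρ = 0.5 between waves. Loss before Wave 3 is equal in both arms at 10%, 20% or 30%. In the PRIMARY arm it depends on the Wave 2 score with log-odds 1 per SD; in the other arm it is random. Only the 10% comes from the document; the rest is assumed.

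Selection on Wave 2 shifts the completers' Wave 2 mean by some amount s and their Wave 3 mean by ρs, so the bias in the Wave 2-to-3 change is (1 − ρ)s in absolute size. The simulated s is 0.087, 0.177 and 0.243 SD. This gives 0.5 × 0.087 = 0.044, 0.5 × 0.177 = 0.089 and 0.5 × 0.243 = 0.122.

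The standard error of the difference in change with n completers per arm is √[2 × 2(1 − ρ) / n] = √(2 / n).

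| Loss | Completers per arm | Simulated bias in change (SD) | Standard error (formula) | Rejection of a true null by the interaction test |
|---|---|---|---|---|
| 10% | 47.7 | 0.04 | 0.205 | about 6% |
| 20% | 42.4 | 0.08 to 0.09 | 0.217 | about 7% |
| 30% | 37.1 | 0.12 to 0.13 | 0.232 | about 8% |

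The ranges span separate simulation runs. Simulated standard errors are about 0.21 to 0.23. Maximum likelihood on all observed waves keeps the bias at about 0.01 SD or less in every row. When loss depends on Wave 2 in the same way in both arms, the complete-case bias is also near zero and rejection stays at about 5%.

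**4. Precision.** Set the noncentrality so that N = 42 or N = 106 gives 80% power at α = 0.05. Complete-case power is then about 79 to 80% at 10% loss, 74 to 75% at 20% and 68 to 69% at 30%. A mixed model recovers little of this for the Wave 2-to-3 contrast, because a missing Wave 3 remains missing. The case for changing the method rests on the inclusion rule and on bias, not on power.

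**The case against.** The strongest reply is that the article nowhere prescribes complete-case analysis. Deletion is the default behaviour of the named test, not a stated rule, and an ANOVA after multiple imputation would keep everyone. A condensed article may leave the details to a fuller plan. That stands in part: the point is not that the plan orders deletion. But the article does fix a test, and that test conflicts with the article's own inclusion rule. A sentence that says only that imputation will be considered does not resolve the conflict.

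It is also fair to say that the harm needs outcome-dependent loss that differs by arm, which nothing in the article predicts, and that the effect is small at the stated 10% loss. Both are accepted.

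A reader might infer three stronger claims that the document does not support.

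- *That stopping HYPE removes a participant's earlier data.* Measures ties Wave 3 to enrolment and to time since the start of treatment, so someone who stops early is still due a Wave 3 assessment.
- *That the sections disagree on who has a Wave 3.* The Objectives wording, "Scores on the specified outcome variables after 10 weeks of HYPE treatment (Wave 3) will be compared", is ordinary shorthand for the same time point. No section makes Wave 3 conditional on remaining in treatment.
- *That the withdrawal rule is breached.* Ethics and dissemination says "the data that has been collected thus far will be used in the study, unless the participant specifically requests their data to be deleted", but it does not promise use in every analysis. Wave 1 and 2 scores of people who leave later still enter the objective 1 ANCOVA.

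**Conclusion.** The point holds as a mismatch between the inclusion rule and the objective 2 test, with no committed method to bridge it. Its likely numerical effect is modest: about a fifth of a standard error at 10% loss (0.04 / 0.205 = 0.20) and roughly 0.4 to 0.6 of one at 20 to 30% (0.08 / 0.217 = 0.37; 0.13 / 0.232 = 0.56). These figures rest on the assumed one-arm mechanism, correlation and arm size. The document gives no Wave 3 loss rate beyond the general 10% from the feasibility study. Only the nested HYPE objective is affected; the main Wave 1 to Wave 2 comparison does not use Wave 3. The change is worth making because it brings the analysis into line with the plan's own rule at almost no cost.

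**What to change.** Replace the repeated-measures ANOVA for objective 2 with a likelihood-based linear mixed model: group, wave and group by wave, with an unstructured covariance across the three waves. Use every observed wave from all participants who start HYPE. Alternatively, keep the ANOVA and commit firmly to multiple imputation beforehand, with an imputation model that contains all three waves and is fitted separately by arm. Either route meets the inclusion rule, and both assume that missingness depends only on observed data. In both cases, report Wave 3 availability by arm.

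The cost is a change of wording and analysis code. No assessment is added. Data collection is predicted to run until April 2026, so the choice can be recorded before the objective 2 analysis is carried out.
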